### Measures and questionnaire

2.4

A questionnaire was developed to assess children’s knowledge related to CSA prevention, based on a comprehensive review of international educational and preventive interventions. A group of experts selected the most important questions from a validated questionnaire (test–retest reliability *r* = 0.92, internal consistency Kuder–Richardson *r* = 0.83, and validity with the Children’s Knowledge of Abuse Questionnaire-Revised *r* = 0.76) (35). The experts retained 14 questions on topics that impact the prevention of such violence (Table 1). Following the development of the measurement instrument, two cognitive laboratories (36) will be conducted: one in an urban public elementary school and another in a rural public elementary school. These cognitive laboratories will facilitate the necessary adjustments to the questions, ensuring each one is clear and comprehensive for children. Subsequently, a pilot test will be conducted to evaluate both the IVR intervention and the knowledge questionnaire. Any necessary modifications to the instrument will be implemented considering this pilot phase. Finally, upon the implementation of the intervention, each participant will be administered the questionnaire. To ensure complete comprehension by the children, a member of the research team will read every question aloud.

**Table 1 tab1:** Questionnaire created for measuring knowledge for the prevention of child sexual abuse (CSA).

1) Imagine that someone tells you they are planning a surprise party for your teacher and insists on keeping it a secret. Wouldn’t you want to help them out and keep it under wraps?		
Yes	No	I do not Know
2) Do children have the right to go to the doctor when they are not feeling well, just like adults?		
Yes	No	I do not Know
3) If someone pinches you or squeezes your arm really hard, is it okay to say you do not like it and then walk away?		
Yes	No	I do not Know
4) If a family member or a friend wanted to touch your private parts, would you feel comfortable telling a trusted person?		
Yes	No	I do not Know
5) If someone touches your body in a way that makes you feel uncomfortable, do you think it’s your fault?		
Yes	No	I do not Know
6) Is it okay for someone who loves you to give you a hug that makes you feel good?		
Yes	No	I do not Know
7) If someone were to touch you in a way that made you feel a bit uneasy and then asked you to keep it a secret, would you keep it a secret?		
Yes	No	I do not Know

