8) If something happened to you that you are embarrassed, afraid, or ashamed of, would you tell someone you trust?		
Yes	No	I do not Know
9) If someone were to touch you in a way that made you feel uncomfortable and then told you that they would hurt your family, would you tell someone you trust?		
Yes	No	I do not Know
10) Do all children have the right to live free of violence?		
Yes	No	I do not Know
11) Both boys and girls can play with any toy they want, regardless of whether it’s a “boys’ or girls’ toy.		
Yes	No	I do not Know
12) You are such a unique and special person. You are loved just as you are, and you have so much value.		
Yes	No	I do not Know
13) Should you always greet an adult person with a kiss or a hug, even if you feel uncomfortable greeting him or her?		
Yes	No	I do not Know
14) If a grown-up listens to you, believes you, makes you feel happy, takes care of you, and does not hurt you, can we say that they are a person you can trust?		
Yes	No	I do not Know

Three knowledge measurements will be taken in both groups.

Intervention Group: Measurement will be taken prior to the intervention (baseline), immediately after the IVR session, and 15 days later.Control Group: Measurement will be conducted at baseline, followed by two follow-up phases: 20 min after the initial measurement and 15 days later (Figure 1).

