### Statistical analysis

2.7

A descriptive analysis of the baseline characteristics (schools and students) will be conducted. Continuous variables will be reported using the mean and standard deviation. Categorical variables will be presented as frequencies and percentages. We will employ a Propensity Scores matching strategy to create comparable intervention and control groups based on observed baseline covariates.

Following the matching, covariate balance will be assessed using the t-test for continuous variables and the chi-square test for categorical variables. This post-matching evaluation is essential for validating the matching procedure and confirming the similarity of initial group characteristics. The impact of the intervention will be evaluated using a mixed-effects generalized least squares model. This model is specifically selected to address the hierarchical data structure (students nested within matched schools) and the study’s inherent cluster randomized design. The model will include fixed effects at the matched pair level and random effects at the student level. The analysis will also explore subgroup effects by assessing how the intervention’s impact varies across key demographic variables, including school location (rural vs. urban) and school type (public vs. private).

If the percentage of missing data is less than 5%, imputation is not necessary; biases are minimal if the data are mostly Missing Completely at Random (MCAR). The analysis can be performed with complete cases (listwise deletion). If the percentage of missing data is greater than 5%, missing values will be handled primarily by multiple imputation using chained equations (MICE) that account for the hierarchical data structure (school and individual levels). Sensitivity analyses (complete-case, inverse probability weighting, and, if needed, MNAR-based models) will be performed. The proportion of missing data per variable and cluster will be reported. The primary outcome will be analyzed at a two-sided *α* = 0.05. For multiple comparisons, the false discovery rate (FDR, Benjamini–Hochberg) or Bonferroni corrections will be applied as appropriate. All estimates will be presented with 95% confidence intervals and both raw and adjusted *p*-values The whole analysis will be done using Stata 17.0 software (College Station, TX).

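### The 5% rule for listwise deletion has no unit, so it does not cap how many children are dropped; one primary method should apply at any level of missingness

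*Protocol article*

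**What the plan says.** Section 2.7 of the protocol article sets a two-branch rule. Below the cut-off: "If the percentage of missing data is less than 5%, imputation is not necessary", with the justification that "biases are minimal if the data are mostly Missing Completely at Random (MCAR" and the consequence that "The analysis can be performed with complete cases (listwise deletion". Above it, "missing values will be handled primarily by multiple imputation using chained equations (MICE", with account taken of school and individual levels. The next sentences add "Sensitivity analyses (complete-case, inverse probability weighting, and, if needed, MNAR-based models) will be performed" and "The proportion of missing data per variable and cluster will be reported".

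The same section plans a mixed-effects model with random effects for students. Section 2.4 describes the data that the rule will act on: "Three knowledge measurements will be taken in both groups" and "The experts retained 14 questions on topics that impact the prevention of such violence".

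**The concern.** Two features of the rule are weak.

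First, the percentage has no denominator. It could count item values, wave scores, child-waves or children. Listwise deletion acts on whole records, and if the record is the child, a low rate per variable or per wave can remove a clearly larger share of children. The only unit the section names is for reporting (per variable and cluster), not for the trigger. Exactly 5% falls in neither branch.

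Second, the amount of missing data is used as if it spoke to the mechanism. The low-bias claim is conditional on the data being mostly MCAR, and the rule includes no check of that condition. The primary handling (complete cases or imputation) is also unknown until missingness has been seen.

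At stake are observed scores thrown away although the planned model could use them, and a treatment effect that could be biased if the deleted children differ in knowledge, or in distress that differs by arm.

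**Working it through.** **Inputs.** From the article: three measurements and 14 items (2.4), so 3 × 14 = 42 responses per child; 12 schools per arm, ICC 0.15, 80% power, significance 0.05 and 324 children per arm (2.1); two-sided testing (2.7). The article gives no expected missing rate, so every rate below is an assumption, kept under 5%.

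**The plan's own figure.** No loss from deletion is stated; the only related figure is 324 per arm. The means and SDs behind it are not printed, so it can be back-solved but not reproduced.
- Children per school: 324 / 12 = 27. Design effect: 1 + 26 × 0.15 = 4.9. Effective n: 324 / 4.9 = 66.1.
- Detectable difference: (1.960 + 0.842) × √(2 / 66.1) = 0.487 SD.
- Forward check with an assumed 0.49 SD: 66 per arm under individual randomisation; 66 × 0.85 × 12 / (12 − 66 × 0.15) = 320.6, or 26.7 per school, rounded up to 27, giving 324. The figure is consistent with the stated inputs.

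**Share dropped under different readings.**

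| Reading | Assumed missingness | Dropped |
|---|---|---|
| 5% counts children with any missing value | under 5% | under 5% of children |
| Only the day-15 score missing, deletion by child | 4% | 4% of children |
| Wave scores missing independently at three waves, deletion by child | 4.9% per wave | 1 − 0.951³ = 14.0% of children |
| Deletion by child-wave | 4.9% per wave | 4.9% of wave records; the child's other waves stay |

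**Upper bound at item level.** If a child were deleted for any one blank among 42 independent responses, the share lost is 1 − (1 − p)^42: 19.0% at p = 0.5%, 34.4% at 1%, 57.2% at 2%, 82.0% at 4% and 87.9% at 4.9%. Blanks tend to cluster within children. A beta-binomial with intra-child correlation ρ gives 1 − B(a, b + 42) / B(a, b), where a = p(1 − ρ)/ρ and b = (1 − p)(1 − ρ)/ρ. At p = 4.9% the loss is then 54.8%, 30.6%, 19.3% and 9.4% for ρ = 0.1, 0.3, 0.5 and 0.8.

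**Power.** Start from 80% at 0.487 SD, keep all schools, and let a share L of children be lost evenly.
- L = 14%: 23.2 per school; design effect 1 + 22.2 × 0.15 = 4.33; effective n 278.6 / 4.33 = 64.3; power 78.9%.
- L = 34.4%: 17.7 per school; design effect 3.51; effective n 212.5 / 3.51 = 60.6; power 76.5%.

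With schools fixed and ICC 0.15, moderate loss of children costs little power.

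**Bias.** Deletion that depends only on terms in a correctly specified model, such as arm or matched pair, does not by itself bias the effect. Deletion related to knowledge, or to distress that differs by arm, can. The article makes the second plausible: Ethical aspects (2.5) expects some discomfort or anxiety with headsets and excludes the data of children who stop. Before the third measurement only the intervention arm wears headsets, and these exclusions may never count towards the 5%. No figure in the article allows the bias to be sized. A likelihood-based mixed model tolerates missingness that depends on a child's other observed scores; deletion by child does not in general.

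**The case against.** The strongest reply is that the article never says the deleted case is the child. In a repeated-measures layout with student random effects, the incomplete record is naturally one child-wave, and the child's other waves stay in. If the 5% means children with any missing value, heavy losses cannot occur under the deletion branch at all, because they would trigger imputation. Both readings are open, and that is the difficulty: the text does not choose.

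A reader might infer that the rule would delete 19% to 82% of children. The article does not support that as an expectation. It needs a per-value reading of the 5%, deletion by child over 42 responses, independent blanks and no scoring rule that tolerates a blank. Questions are read aloud and each offers a don't-know answer, which should keep blanks rare. How a score is formed with a missing item is a detail that an article may leave to the full plan, so its absence is not held against this one.

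The first follow-up takes place on the day of baseline for controls (20 minutes later) and straight after the headset session in the intervention arm. Absence should therefore fall mainly on day 15, nearer the 4% row than the 14% row.

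A reader might also infer that the analysis could be picked to suit the result. It could not on this rule: the switch is pre-specified and depends on missingness, not on the treatment effect.

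Finally, sensitivity analyses and reporting of missingness are planned. That counts in the plan's favour. But the sensitivity sentence follows the above-5% branch without saying whether it also covers the lower one, and sensitivity analyses do not repair the choice of primary method.

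**Conclusion.** The point holds in a limited form. The rule permits listwise deletion as primary handling under a threshold that has no unit and does not establish MCAR. On a per-variable or per-wave reading, 5% does not cap the share of children dropped. Under assumed rates the plausible size runs from about 4% (day 15 only) to about 14% (4.9% at each of three waves, independent, deletion by child), and stays under 5% if the unit is children with any missing value. The 42-response figures are an upper bound under independence only.

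Power is not the issue: about 79% instead of 80% at 14% loss. What remains is avoidable loss of observed scores and a possible bias of unknown size. The documents do not show that such bias will occur, only that the rule gives no protection against it. The point is worth acting on because a better primary analysis is already within the planned model.

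**What to change.** Remove the 5% switch from section 2.7. State instead that, whatever the percentage missing:

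- The primary analysis is the mixed model fitted by maximum or restricted maximum likelihood to all available child-wave scores of all children in the randomised schools, without listwise deletion, and valid under MAR. Baseline is best treated as one of the repeated scores, so that a child without it is not dropped. The article calls the model generalised least squares, so the estimation method should be named.
- Multilevel MICE, complete-case and MNAR analyses are sensitivity analyses at any level of missingness; the planned inverse probability weighting can stay among them.
- Missingness is reported per variable and cluster as planned, and also by arm and wave. Children excluded after stopping the headset session are counted separately.

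The full plan should hold the rule for scoring a questionnaire with blank items. Prorating when at least 12 of 14 items are answered is one example, not a value drawn from the article.

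The cost is analysis wording, and slightly more work if few data are missing. The change is best made before outcome data are seen.

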**Figure 1 fig1:**
[figure not shown]
Study design.

For school selection, a list will be requested from the Ministry of Education, focusing on municipalities with a gender violence alert designation. This designation indicates emergency governmental actions to confront and eradicate femicide and the disappearance of women. A random sampling of schools will then be conducted from this list. Prior to randomization, schools will be paired 1:1 based on specific characteristics (e.g., size, type, locality).

The required sample size for the intervention was calculated using the clustersampsi command from the STATA statistical software package, which is designed for estimating sample sizes in cluster randomized trials. The mean knowledge scores (and standard deviations) of the control and intervention groups were included, setting the number of clusters at 12 schools per arm (due to the operational capacities of the work team) (33). The intraclass correlation value was set at 0.15 (34), the power at 80%, and the statistical significance at 0.05. This resulted in a minimum sample size of 324 children per arm. Following the selection of the participating elementary schools, the randomization unit will be the schools as a whole. Specifically, all eligible children in the second and third grades within a selected school will participate in the study.

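### Where family-wise control is intended, the Bonferroni option in section 2.7 gives up power that Holm would keep under the same guarantee

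*Protocol article*

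**What the plan says.** Section 2.7 (Statistical analysis) is the only place in the protocol article that deals with multiplicity. For multiple comparisons it names two corrections, Benjamini-Hochberg false discovery rate control "or Bonferroni corrections will be applied as appropriate". The same paragraph says "The primary outcome will be analyzed at a two-sided" alpha of 0.05, and on reporting: "All estimates will be presented with 95% confidence intervals and both raw and adjusted" p-values.

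Two sources of several comparisons are visible. Section 2.4 states "Three knowledge measurements will be taken in both groups", which gives two post-baseline contrasts between arms: immediately after the session (20 minutes after the first measurement in controls) and 15 days later. Section 2.7 also plans to explore effects by "school location (rural vs. urban) and school type (public vs. private").

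The sample size paragraph in section 2.1 sets "the power at 80%, and the statistical significance at 0.05", with no adjustment of that level for multiple tests.

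**The concern.** Bonferroni is chosen when the chance of any false claim is to be held at 5%. Holm does the same job at the same level, under any dependence between the tests. It begins with the Bonferroni step. Only after a rejection does it relax the threshold for the remaining tests, so it can never reject fewer hypotheses. Naming Bonferroni therefore forgoes power with no gain in protection.

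What is at stake is the ability to confirm the effect at both follow-ups. The design has limited room: "setting the number of clusters at 12 schools per arm" was dictated by operational capacity, and "The intraclass correlation value was set at 0.15". Power recovered through the choice of procedure costs no schools.

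**Working it through.** **Inputs from the article**
- Two-sided alpha 0.05 (sections 2.1 and 2.7) and 80% power (section 2.1).
- Three measurements, so two post-baseline contrasts (section 2.4).
- 12 schools and 324 children per arm, intraclass correlation 0.15 (section 2.1).

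**Assumptions, because the article gives no figure**
- The family is the two follow-up contrasts.
- Each contrast has the effect that gives 80% power at 0.05.
- The two test statistics are normal, with correlation 0.5, 0.7 or 0.85.

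**The plan's own figure.** The means and standard deviations behind 324 are not printed, so it cannot be reproduced forward. Working back:
- 324/12 = 27 children per school.
- Design effect 1 + 26 × 0.15 = 4.9.
- Effective size 324/4.9 = 66.1 per arm.
- Standardized difference detectable with 80% power at 0.05: 2.80 × √(2/66.1) ≈ 0.49.

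The comparison below does not depend on this value. It needs only the planned effect in standard errors: 1.960 + 0.842 = 2.80.

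**One contrast at the Bonferroni level.** With two tests the threshold is 0.05/2 = 0.025, critical value 2.241. Power is Φ(2.80 − 2.24) = 0.71, against the planned 0.80.

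**Rules for two tests**
- Bonferroni declares both if both p ≤ 0.025.
- Holm declares both if the smaller p ≤ 0.025 and the larger p ≤ 0.05.
- Benjamini-Hochberg declares both if the larger p ≤ 0.05.
- Bonferroni and Holm declare at least one under the same condition: the smaller p ≤ 0.025.

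Example: with p = 0.02 and 0.04, Bonferroni declares one contrast and Holm both.

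**Simulation (bivariate normal, mean 2.80 for each contrast)**

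| Correlation | Both: Bonferroni | Both: Holm | Gain (points) | Both: Benjamini-Hochberg | At least one: Bonferroni = Holm |
|---|---|---|---|---|---|
| 0.5 | 57.3% | 67.8% | 10.5 | 68.8% | 85% |
| 0.7 | 60.7% | 70.1% | 9.4 | 71.4% | 82% |
| 0.85 | 63.6% | 72.1% | 8.5 | 73.9% | 79% |

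**Family-wise error of Benjamini-Hochberg for these two tests.** At correlation 0.5, 0.7 and 0.85 it is 4.8%, 4.6% and 4.3% when both effects are null, and 4.3%, 4.0% and 3.8% when one is real. All are below 5%.

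**The case against.** Four objections deserve an answer.

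**Bonferroni is valid, and preferring Holm is a matter of efficiency.** This stands, and the point is made only as one of efficiency.

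**The gain appears only if both follow-ups are to be claimed.** This also stands. For at least one significant contrast the two procedures are identical, and the article does not say that both must succeed.

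**Holm is not the most powerful option already on the page.** Benjamini-Hochberg does slightly better in the table, and with p = 0.03 and 0.04 it declares both contrasts while Holm, like Bonferroni, declares neither. That is correct. However, its family-wise protection for two tests relies on a condition on their dependence, and Holm's does not.

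**Holm has no simple matching simultaneous confidence intervals.** True, but section 2.7 promises 95% intervals and does not call them simultaneous, so nothing promised is lost.

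A reader might also infer more than the article supports:
- *That Benjamini-Hochberg weakens protection at the two follow-ups.* With two tests it coincides with Hochberg's procedure, which holds the family-wise error at 5% or less under positive correlation, as the figures above show. In larger families with some real effects it does not bound that error. But the article defines no such family, and the subgroup analyses are described as exploratory.
- *That leaving the choice open is itself an error.* Assigning procedures to families is detail that an article commonly leaves to the full analysis plan, which is not shown. Reporting raw p-values also lets readers apply either correction themselves.
- *That the corrections could give opposite findings.* They can differ only on significant versus not significant, never on the direction of effect.

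**Conclusion.** The point holds as a small, cost-free improvement. Where section 2.7 intends family-wise control, Holm gives Bonferroni's guarantee and never rejects less. For two follow-up contrasts at the planned effect, the chance of confirming both rises by roughly 8 to 10 points, from 57–64% to 68–72%. The chance of confirming at least one stays at about 79–85%.

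Holm's dominance over Bonferroni needs no assumption. The size of the gain does: it rests on a two-contrast family, on both effects being real and as large as planned, on normal test statistics and on the assumed correlation. Whether the follow-up contrasts come under the correction at all is not stated, since the primary outcome has its own 0.05 level and the article does not tie it to one follow-up.

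**What to change.** In section 2.7, replace Bonferroni with Holm for any comparisons on which effectiveness will be claimed. Keep Benjamini-Hochberg for the exploratory subgroup results by school location and school type, and label them as exploratory. Report the Holm-adjusted p-values next to the raw ones, with the ordinary 95% intervals already promised.

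The change is one sentence, made before outcome data are seen. It needs no change to the sample, the measurements or the model. The one thing given up is Bonferroni's easy route to simultaneous intervals, which the article does not promise.

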## Discussion

3

Research indicates that educational interventions successfully enhance individuals’ knowledge of sexuality. However, determining the extent to which these interventions actually prevent CSA remains challenging due to the paucity of empirical data on program effectiveness in real-world settings (22, 37). The advent of the VLE has enabled the rigorous evaluation of digital tools in CSA prevention. Studies utilizing VLEs have demonstrated a significant enhancement of knowledge and key conceptual understanding related to CSA prevention in experimental groups (38). Therefore, there is a compelling need to strengthen children’s learning through an educational intervention based on IVR. Immersive Virtual Reality has been shown to have positive effects on knowledge retention, motivation, and learning outcomes (39).

“Pinta tu Raya ASI” incorporates didactic objects to provide users with unique, practical experiences that are not feasible in the physical world seeking an increase in knowledge of key topics. The system effectively represents realistic scenarios while eliminating physical risks and allowing for the precise regulation of conditions, ensuring suitable and safe presentation for the training group. The intervention is innovative, captivating, and highly relevant for children in the second and third grades, as it utilizes cutting-edge technological tools. It is evident that learning reinforced through IVR will play a pivotal role in strengthening children’s understanding of related textbook topics. Furthermore, implementing the intervention in the second and third grades is imperative because these children are within the age range associated with the highest risk of CSA victimization (9, 21, 22). It is important to acknowledge, however, the potential for expanding the intervention’s scope beyond elementary school children to encompass a triad of student-teacher-family training. This comprehensive approach will be considered during later developmental stages of our project to maximize CSA prevention efforts.

